### Participant timeline {13}

The participant timeline is shown in Table 1 and the flow diagram in Fig. 1. All participants will have a home visit to collect data at baseline and 1 and 3 months after baseline. Enrollment began in May 2021 and is estimated to end in March 2023.

**Table 1 Tab1:**
[figure not shown]
SPIRIT standard protocol items with participant schedule of enrolment, interventions, and assessments

The table is adapted based on the SPIRIT recommendations [23]

**Fig. 1 Fig1:**
[figure not shown]
Flow of participants

### Sample size {14}

In our study, the primary outcome, HRQoL, is measured using the EuroQoL EQ-5D-5L questionnaire. However, our sample size is calculated based on results from a Japanese study investigating the effect of nutritional support combined with exercise on several outcomes including HRQoL measured using the chronic respiratory disease questionnaire among stable COPD patients. The chronic respiratory disease questionnaire consists of four domains (dyspnea, fatigue, emotional, and mastery) with 20 items in total. Each item is scored on a 7-point scale. There are no reports of a clinical relevant change/difference in the total HRQoL score of the chronic respiratory disease questionnaire. In the Japanese study, a 10-point higher total HRQoL score was reported in the intervention group compared to the control group (109 vs. 99, *p* = 0.04) at the end of the intervention with a standard deviation of 17 points [24] as used in our sample size calculation. With an estimated drop-out rate of 20%, the inclusion of 60 participants in each group, will provide a power of 0.8 at a significance level of 0.05.

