### Outcomes {12}

#### Primary outcome

The primary outcome is HRQoL measured using the EuroQoL EQ-5D-5L questionnaire [18], a generic health status questionnaire that has been validated in individuals with COPD [19].

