#### Sensitivity analysis

Additionally, linear mixed models that also include relevant covariates (as fixed effects) will be fitted to adjust for observed baseline imbalance (if needed). Relevant covariates include age, BMI, sex, pulmonary function, and the number of comorbidities.

For all fitted linear mixed models, the two estimated mean changes from baseline to 3 months (for both intervention groups) as well as the estimated mean difference in change from baseline to 3 months will be reported together with the corresponding 95% confidence intervals and *p* values. Statistical significance will be declared whenever the *p*-value is below 0.05.

Where appropriate, outcome values will be transformed prior to the statistical analysis.

For categorical secondary or other outcomes data will be analyzed by means of logistic mixed-effects regression models that include an intervention group-time interaction as a fixed-effects term and block and participant-specific random effects. Baseline values will be part of the outcome. The estimated difference in change from baseline to 3 months will be reported as a ratio of odds ratios together with the corresponding 95% confidence interval and *p* value.

Statistical analyses will be carried out using STATA/IC version 17.0 (StataCorp LP, USA). Specifically, the commands XTMIXED and XTMELOGIT will be used for fitting linear mixed models (using residual maximum likelihood estimation) and logistic mixed-effects regression models (using maximum likelihood estimation), respectively.

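### The stated 80% power is not established for EQ-5D-5L: it was calculated from another questionnaire in a nutrition-plus-exercise study

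*Protocol article*

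**What the plan says.** All references are to the protocol article.

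- **Primary outcome:** "The primary outcome is HRQoL measured using the EuroQoL EQ-5D-5L questionnaire". The abstract defines the comparison as a difference between groups 3 months after baseline. The section on health-related quality of life describes two EQ-5D-5L scores, a country-specific index (Danish range −0.624 to 1.000) and a 0–100 self-rating. It gives no target difference or SD for either.
- **Sample size {14}:** this section repeats that "the primary outcome, HRQoL, is measured using the EuroQoL EQ-5D-5L questionnaire" and then discloses that "our sample size is calculated based on results from a Japanese study investigating the effect of nutritional support combined with exercise". In that study the outcome was "HRQoL measured using the chronic respiratory disease questionnaire among stable COPD patients", and "a 10-point higher total HRQoL score was reported in the intervention group compared to the control group" (109 vs. 99) at the end of the intervention, with an SD of 17. The section adds that no clinically relevant difference has been reported for that total score. It then assumes 20% drop-out and concludes that "the inclusion of 60 participants in each group, will provide a power of 0.8 at a significance level of 0.05".
- **Intervention description {11a}:** there are four elements (nutritional plan, regular contact, adherence support, weight diary). Exercise is not among them.
- **Statistical methods {20a}:** for the linear mixed models, the mean change in each group "as well as the estimated mean difference in change from baseline to 3 months will be reported", with 95% confidence intervals and p values.

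**The concern.** The power sentence is unqualified and reads as a property of this trial's primary comparison. Its inputs belong to a different instrument, a 20-item respiratory questionnaire, and to a different treatment. The section does not argue that a standardised effect of 0.588 carries over to a generic five-question instrument without an exercise component. Because the section also says that no relevant difference is known for the borrowed score, the planning effect is an observed result and not a threshold of clinical relevance.

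What is at stake is how the result is read. If the trial is non-significant, a stated 80% power invites the conclusion that a relevant effect on quality of life has been largely ruled out. No relevant EQ-5D-5L difference was ever specified, so that conclusion would have no basis.

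**Working it through.** **Inputs from the protocol.** Difference 10 points, SD 17 points, alpha 0.05, power 0.8, drop-out 20%, 60 per arm. The protocol does not say whether the test is one- or two-sided. Two-sided is assumed, because the one-sided version gives 36 per arm (45 after drop-out), which does not fit the stated 60.

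**1. Reproducing the stated number.**
- Standardised effect: d = 10/17 = 0.588.
- Normal approximation: n = 2(1.96 + 0.8416)² / 0.588² = 45.4, so 46 per arm; 46/0.8 = 57.5, so 58.
- Two-sample t-test: n = 46.3, so 47 per arm; 47/0.8 = 58.75, so 59.
- Stated: 60 per arm, which leaves 60 × 0.8 = 48 evaluable. At d = 0.588, t-test power is then 0.814.

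The calculation is sound for the borrowed score.

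**2. What 48 evaluable per arm can detect on any continuous score.** By t-test, 80% power needs d = 0.578 (0.572 by the normal approximation). Power by assumed true standardised effect:

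| Standardised effect | Power (t-test) |
|---|---|
| 0.2 | 16% |
| 0.3 | 31% |
| 0.4 | 49% |
| 0.5 | 68% |
| 0.588 | 81% |

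**3. In EQ-5D-5L index units.** The protocol gives no SD, so those below are assumptions. Detectable difference = 0.578 × SD.

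| Assumed SD of index | Detectable difference |
|---|---|
| 0.15 | 0.087 |
| 0.20 | 0.116 |
| 0.25 | 0.144 |

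If the primary score is the 0–100 self-rating, the same 0.578 × SD applies with that score's SD.

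**4. The reported contrast.** For a pure difference in change, SD(change) = SD × √(2(1 − ρ)), where ρ is the baseline-to-3-month correlation. The protocol gives no ρ, so the values below are assumptions. The detectable difference, in units of the single-visit SD, is 0.578 × √(2(1 − ρ)):

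| Assumed ρ | Detectable difference | Power at d = 0.588 |
|---|---|---|
| 0.3 | 0.578 × 1.183 = 0.68 SD | 67% |
| 0.5 | 0.578 × 1.000 = 0.58 SD | 81% |
| 0.7 | 0.578 × 0.775 = 0.45 SD | 96% |

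A baseline-adjusted contrast has residual SD = SD × √(1 − ρ²), so it never does worse than the 3-month comparison.

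**The case against.** The strongest reply is that nothing is hidden. The same paragraph names the source study, its questionnaire and its exercise component, and the plan already reports 95% confidence intervals and commits to publishing inconclusive results. Borrowing a standardised effect when no direct data exist is also common practice. This stands as far as it goes: disclosure of the source needs no fix. It does not cure the final sentence, which asserts a power for this trial with neither an EQ-5D-5L difference or SD nor an argument for the transfer.

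Three stronger readings are tempting, and the documents do not support them.

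- **That the trial lacks 80% power.** Without an EQ-5D-5L effect or SD the power is unknown. It reaches 80% if the true standardised difference is about 0.58 or more.
- **That the calculation used the wrong contrast.** The abstract defines a group difference at 3 months, the same type as the source study's end-of-intervention difference. Under randomisation the expected difference in change equals the expected difference at follow-up. The change contrast loses power only if the correlation is below about 0.5 and gains power above it.
- **That the source effect is too imprecise to use.** One could back-calculate that study's size and confidence interval from p = 0.04 and SD 17. This would assume equal arms, a common SD and an unadjusted t-test, none of which the protocol states.

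**Conclusion.** The point holds in this form: the 0.8 is correct for a standardised effect of 0.588 on the chronic respiratory disease questionnaire after nutrition plus exercise, and it is not established for EQ-5D-5L in this trial. What the trial can claim at its fixed size is 80% power for about 0.58 SD at 3 months. Power falls to 68%, 49% and 31% if the true effect is 0.5, 0.4 or 0.3 SD.

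These figures assume a two-sided 0.05 t-test with 48 evaluable per arm. The index-point values rest on assumed SDs, and the figures for the change contrast rest on assumed correlations. The sample size arithmetic itself is not in error. What is wrong as written is the outcome to which the power figure is attached.

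**What to change.** Keep 60 per arm and replace the power sentence in Sample size {14} with wording such as:

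*With 48 evaluable per arm (two-sided 0.05) the trial has 80% power for a standardised difference of about 0.58 in the EQ-5D-5L score at 3 months; power is about 31%, 49% and 68% at 0.3, 0.4 and 0.5 SD.*

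Then:

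1. Name the score to which this applies, the country-specific index or the 0–100 self-rating.
2. Translate 0.58 SD into that score's units, using the pooled baseline SD of enrolled participants without regard to arm.
3. Note that for the difference in change reported under Statistical methods {20a} the detectable difference depends on the baseline-to-3-month correlation (about 0.68, 0.58 and 0.45 SD at assumed values of 0.3, 0.5 and 0.7).
4. State that a non-significant result will be read from the 95% confidence interval and not as 80%-powered evidence of no effect.

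The cost is rewording, one arm-blind SD calculation and a less favourable stated figure. It needs no extra participants, no unblinding and no change to the analysis.

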### Recruitment {15}

Participants are recruited from the pulmonary ward and the outpatient clinic at the Department of Pulmonary and Infectious Diseases, Copenhagen University Hospital, North Zealand, Denmark. Potential participants are identified in the following three ways: (1) lists of individuals with COPD followed in the pulmonary outpatient clinic, (2) hospitalized in the pulmonary ward, or (3) through visits in the pulmonary outpatient clinic. The list of individuals with COPD is generated by a person from the analysis team at the hospital from the electronic medical journal (Sundhedsplatformen, EPIC, USA) and contains individuals in contact with the pulmonary outpatient clinic within a defined period (e.g., the last 12 months) with IC-10 diagnosis codes from DJ439 to DJ449. Potential participants are chosen from the generated list using random numbers generated by the statistical program R [25]. The randomly chosen individual is screened for eligibility and participants with potential eligibility will receive a letter with information about the project. Recruitment from the list will be the primary recruitment method. If it is considered necessary to use supplemental recruitment methods, the other two methods will be used. The study coordinator will visit patients during a hospitalization in the pulmonary ward and shortly introduce the project through a short oral presentation and the information letter. Finally, the nurses from the outpatient clinic have been encouraged to hand over the information letter during visits when an individual is considered potentially eligible (BMI < 25 kg/m^2^) to participate in the project. All identified potential participants will receive a phone call from the study coordinator with further information about the project.

After receiving an oral informed consent and if the inclusion criteria are met, a home visit will be scheduled. At the first home visit, informed written consent will be obtained, baseline data will be collected, and group allocation will be revealed in the abovementioned order.

## Assignment of interventions: allocation

### Sequence generation {16a}

Participants will be randomly allocated to either intervention or control group using computer-generated block randomization with random group sizes of 2, 4, and 6 (using the R extension package “blockrand”) [26].

### Concealment mechanism {16b}

A file/photo of each allocation by ID number will be saved in a separate folder on a secure network drive. When a participant is enrolled in the study, the study coordinator will open the ID number and the allocation will be revealed.

### Implementation {16c}

The allocation sequence is performed by a person not involved in the project. This person has also performed the concealed allocation by saving a file/photo of each allocation by ID number at a secure folder at a network drive at the hospital. The study coordinator who is blind for the allocation will enroll participants. After the baseline assessment, the group allocation will be revealed for the study coordinator and the participant.

## Assignment of interventions: blinding

### Who will be blinded {17a}

This is an open-label study. The trial coordinator is responsible for all parts of the project including intervention, data collection, data analysis, and dissemination. Though the trial coordinator is blinded during the baseline assessment and data analyses.

### Procedure for unblinding if needed {17b}

Since blinding is not possible after baseline assessment unblinding will not be needed.

## Data collection and management

### Plans for assessment and collection of outcomes {18a}

An overview of the assessment and collection of outcome variables is shown in Table 2. All data collection will be performed by the study coordinator or under special circumstances other trained personnel (a project nurse or a student assistant).

**Table 2 Tab2:** Overview of study outcomes

Assessments	Specific measurements	*Timepoint*			*Mean/median*	*Percent/proportion*	*Type of variable*
		***Baseline***	***1 mo***	***3 mos***			
**Primary outcome**							
Health-related quality of life	EQ-5D-5L	x	x	x	x		Numerical
**Secondary outcomes**							
Hospitalizations	Acute hospitalizations (all causes)		x	x		x	Numerical
Days in hospital	Number of days in hospital (all causes)		x	x	x		Numerical
Other hospital contacts	Acute hospital contacts < 6 h		x	x	x		Numerical
Contact to the outpatient clinic	Contact to the outpatient clinic via phone or visit		x	x	x		Numerical
Mortality	Mortality (number of deaths)		x	x		x	Binomial
Disease-specific quality of life	COPD Assessment Test	x	x	x	x		Numerical
Anxiety and depression	Hospital Acquired Depression Scale	x	x	x		x	Binomial
Muscle strength	Grip strength	x	x	x	x		Numerical
Muscle endurance	30-s chair stand test	x	x	x	x		Numerical
Fat-free mass	Bioelectrical impedance analysis	x	x	x	x		Numerical
Fat mass	Bioelectrical impedance analysis	x	x	x	x		Numerical
Weight	Electronic scale	x	x	x	x		Numerical
Body mass index	Weight (kg)/height(m^2^)	x	x	x	x	x	Numerical/categorical
**Other outcomes**							
Hip circumference	Measuring tape	x	x	x	x		Numerical
Waist circumference	Measuring tape	x	x	x	x		Numerical
Mid-upper arm circumference	Measuring tape	x	x	x	x		Numerical
Exacerbation history	Number of exacerbations	x	x	x	x		Numerical
Oxygen therapy	Yes/no	x	x	x		x	Binomial
General physical activity level	Physical Activity Vital Sign	x	x	x	x		Numerical
Physical activity level	AX3 accelerometers	x		x	x		Numerical
Protein intake	24-h recall	x	x	x			Numerical
Energy intake	24-h recall	x	x	x			Numerical
Difference between energy requirement and intake	24-h recall	x	x	x			Numerical
Difference between protein requirement and intake	24-h recall	x	x	x			Numerical

#### Nutritional risk screening

Nutritional risk is determined using NRS2002 and MNA-SF as part of the recruitment process, at the baseline and 3-months follow-up visits. The NRS2002 is largely used in the hospital setting, whereas MNA is recommended among elderly and frail individuals. The purpose is to provide simple screening tools to detect individuals at risk of undernutrition who might benefit from nutritional support. In the NRS2002, the nutritional risk is defined by the present nutritional status and risk of impairment of present status, due to increased requirements caused by stress metabolism of the clinical condition. The NRS2002 score determines if the patient is at nutritional risk using a scoring system including information about BMI, weight loss, reduced food intake, disease severity, and age. The patient is at nutritional risk if the total score is ≥ 3 [28]. In addition, the MNA-SF is used as supplemented information on nutritional risk. MNA also determines nutritional status based on a scoring system including information on food intake, weight loss, mobility, psychological stress, neuropsychological problems, and BMI. A total score of 12–14 indicates normal nutritional status, whereas a total score of 8–11 and 0–7 indicate risk of malnutrition and malnutrition, respectively [28].

#### Diagnosis of COPD, pulmonary function, and disease severity

The diagnosis of COPD is based on spirometry with a post-bronchodilator FEV_1_/FVC < 0.70 plus symptom burden and risk of exacerbation (group A to D) according to the refined GOLD ABCD assessment tool [15]. Severe COPD is defined as all patients with GOLD grades 3 and 4 (airflow limitation FEV_1_ < 50% of the predicted value) and individuals with GOLD grade 2 with a high symptom and/or exacerbation burden (group B or D). A high symptom burden is based on a CAT score ≥ 10 or a score ≥ 2 on the modified MRC Dyspnea Scale [15]. Information about airflow limitation (pulmonary function) will be obtained from patient files. At baseline and 12 months after baseline, the latest pulmonary function assessment will be registered.

#### COPD assessment test

The COPD Assessment Test contains 8 items with a scoring range of 0–40. The total score indicates the impact level COPD has on the everyday life ranging from low to very high. A total score of 5 is referred to the upper limit of normal in healthy non-smokers, a total score < 10 indicates low impact, 10–20 indicates medium impact, whereas > 20 and > 30 indicate high and very high impact, respectively [31, 35].

#### Health-related quality of life

HRQoL is assessed using the EuroQoL EQ-5D-5L questionnaire [18, 19]. The questionnaire consists of five categories/questions including mobility, self-care, daily activities, pain/discomfort, and anxiety/depression. For each question, there are five possible answers each containing a score from 1 (no problems) to 5 (extreme problems). This will provide a combination of numbers [18] which is translated to a country-specific total index [36]. The lowest Danish index score is − 0.624 and the highest score is 1.000. In addition, the participant is asked to evaluate their own health on a scale from 0 to 100. A score of 100 means the best imaginable health [18].

#### Depression and anxiety

The risk of depression and anxiety will be determined using Hospital Acquired Depression Scale (HADS). HADS contains two subscales to evaluate the risk of anxiety and depression. Each subscale contains 7 items with a total score from 0–21. Risks of anxiety and depression are based on a total score ≥ 8 and a total depression score ≥ 8 or ≥ 5 (if the scale is reduced with one item), respectively [30].

#### Anthropometry and body composition

Height (cm) is based on the latest measurement in their medical record and confirmed by the participant. Weight is measured to the nearest 0.1 kg on an electric scale (TANITA DC 430 SMA, TANITA, Denmark). Body mass index (BMI) is calculated as weight (kg)/height (m^2^). Waist, hip, and mid-upper arm circumference will be measured to the nearest 0.1 cm. Waist circumference will be measured at the midline between the lowest border of the rib cage and the upper border of the iliac crest. Hip circumference will be measured at the broadest level on the hips while participants are standing [37]. Upper-arm circumference will be measured at the right arm at the mid-point between the acromion and the olecranon [38] in sitting or standing posture. Bio-impedance (TANITA DC 430 SMA, TANITA, Denmark) will be used to assess the distribution of total fat-free, fat mass, and indices.

#### Nutritional intake

Nutritional intake will be assessed using 24-h recall [34]. Total protein and energy intake will be calculated using MADlog (MADLOG, Denmark), which is a tool that calculates energy and protein from registered food intake. Protein intake is measured as grams and calories of protein and energy consumed within 24 h, respectively.

#### Functional capacity

##### Muscle strength

Grip strength will be used as an indicator of overall muscle strength and will be measured using a hand dynamometer (SAEHAN DHD-1 Digital Hand Dynanometer, SAEHAN Corporation, South Korea). During the test, the participant will be sitting or standing with the upper arm held along the body with the elbow bent 90 degrees, while the wrist is kept in a neutral position [39]. The test is performed repeated three times on the dominating hand and the highest value is registered. If the participant is uncertain about which hand is strongest, the test will be performed three times on each hand and the highest of all measurements is registered Grip strength is measured in kg.

##### 30-s chair stand test

The 30-s chair stand test is used to evaluate functional ability by measuring lower body strength. The chair will be placed against a wall to secure safety. The participant will sit in the middle of the seat with the feet placed flat on the floor with a shoulder width apart. The arms will be crossed at the wrists and held close to the chest. The test will begin in a sitting position. For 30 s, the participant stands completely up and then completely back down. The score is the number of completed chair stands in 30 s [40].

##### Physical activity

Information on physical activity is collected using the physical activity and vital signs questionnaire [33] and accelerometers (Activity AX3, Newcastle, UK) measuring 7 days from baseline and 7 days from 3-month follow-up.

#### Frailty

Frailty is determined using the FRAIL scale. The FRAIL scale consists of five components each containing a simple question. The components include Fatigue, Resistance, Ambulation, Illnesses, and Loss of weight. The answers will either give 0 or 1 point. A total score of 0 will categorize the participant as robust, while a total score of 1–2 and 3–5 will categorize the participant as pre-frail and frail, respectively [32].

